## Abstract

This protocol describes a randomized controlled trial designed to evaluate the efficacy of Virtual Reality (VR) as a non-pharmacological intervention for pain management in the immediate postoperative period of cardiac and thoracic surgeries. Postoperative pain in these major procedures is often intense and historically managed with high doses of opioids, which are associated with significant side effects and potential dependence. By leveraging the "limited capacity theory of attention," this study uses immersive and passive VR environments to compete with painful stimuli for cognitive resources, thereby aiming to reduce total opioid consumption.

• This protocol establishes a standardized three-arm methodology to compare active VR immersion, passive VR contemplation, and conventional multimodal analgesia in a high-complexity surgical setting.

• It provides a detailed framework for integrating digital distraction technology into intensive care unit (ICU) routines, including a rigorous equipment hygiene protocol to ensure patient safety.

• The study focuses on a specific younger demographic (16–40 years) to evaluate the impact of VR on recovery outcomes, opioid sparing, and patient satisfaction.

## Specifications table

**Table utbl0001:** 

**Subject area**	Medicine and Dentistry
**More specific subject area**	Anesthesiology and Perioperative Medicine.
**Name of your protocol**	Virtual Reality Distraction Protocol for Postoperative Pain Management.
**Reagents/tools**	VR Headsets (Meta Quest), Fruit Ninja 2, Oculus First Contact, Beat Saber, First Hand, YouTube VR
**Experimental design**	Prospective, randomized, open-label, three-arm clinical trial (1:1:1 ratio).
**Trial registration**	ClinicalTrials.gov, NCT07063394
**Ethics**	The study protocol was approved by the Research Ethics Committee of the Hospital das Clínicas da Faculdade de Medicina da Universidade de São Paulo (CAPPESQ - HC-FMUSP). All participants will be informed about the study's objectives, procedures, potential risks, and benefits. We confirm that the relevant written informed consent (Termo de Consentimento Livre e Esclarecido - TCLE) will be obtained from all subjects prior to their inclusion in the study, ensuring the protection of their autonomy and dignity.
**Value of the Protocol**	• This protocol establishes a structured framework for using Virtual Reality (VR) as a low-cost, non-pharmacological intervention aimed at reducing opioid consumption in high-complexity surgical patients. • The study provides a detailed guide for implementing digital distraction in an Intensive Care Unit (ICU) setting, including a rigorous hardware hygiene protocol to ensure patient safety and clinical feasibility. • By comparing active game immersion with passive 360° video contemplation, the protocol helps identify which cognitive distraction mechanisms are most effective in modulating acute postoperative pain.

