## Background

The management of postoperative pain in cardiothoracic surgery remains a critical challenge, as inadequate analgesia more than doubles the risk of postoperative complications (OR 2.56), including respiratory dysfunction and prolonged hospitalization [1]. Furthermore, while opioids represent the analgesic cornerstone, their dose-dependent administration induces adverse events in approximately 20% of patients, precipitating significant morbidity such as respiratory depression, emesis, and long-term dependence [2].

This proposed protocol addresses the clinical need for innovative, non-pharmacological adjuncts to multimodal analgesia. Grounded in the limited capacity theory of attention, highly immersive distractors exhaust finite cognitive resources, modulating shared cortical networks [3] and triggering neurochemical responses, such as endorphin release, to effectively reduce perceived pain intensity [4].

Virtual Reality (VR) provides a superior level of immersion compared to traditional distraction methods, yielding up to an 88% decrease in postoperative pain [5]. Therefore, this study is designed as a proof-of-concept efficacy trial to standardize VR application in the Intensive Care Unit (ICU) setting, targeting patients (16–40 years old) undergoing cardiothoracic surgery. Our primary objective is to evaluate the preliminary clinical efficacy of this multi-session VR protocol on cumulative opioid consumption and pain intensity. It distinguishes itself by evaluating two digital strategies—active gaming, associated with the attenuation of cortical pain-related amplitudes [6], and passive 360° video contemplation—to determine their respective impact on postoperative recovery.

By establishing this early-stage framework, this protocol provides researchers and clinicians with a reproducible model for integrating digital health technology into the perioperative period, emphasizing technical feasibility, equipment hygiene, and patient safety, while gathering preliminary efficacy signals to guide future definitive trials.

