Regarding the experimental arms, Group 2, designated as the passive therapy arm, receives the identical standard clinical protocol supplemented with the Meta Quest VR headsets, providing access to the YouTube VR platform for passive immersion. Crucially, rather than restricting individuals to a standardized preselected playlist, the protocol allows the free selection of 360-degree videos, encompassing nature, space, or cultural events, based on individual preferences. This patient-centered design is methodologically grounded in the premise that cognitive distraction, which is the primary mechanism of action for pain modulation, is maximized when the visual stimulus aligns with the patient's intrinsic interests, thereby ensuring deeper emotional engagement.

Consequently, Group 1 represents the unrestricted enriched therapy arm, receiving the standard clinical protocol along with VR headsets equipped with both the passive YouTube VR content and immersive interactive gaming experiences. These active applications include Beat Saber, First Hand, Fruit Ninja 2, and Oculus First Contact, selected to ensure a diverse range of motor and cognitive engagement. By intentionally allowing free transition between active and passive content, this pragmatic design aims to evaluate whether providing the additional option of interactivity yields superior clinical outcomes and higher protocol adherence compared to the strictly passive device of Group 2. Rather than enforcing a rigid mechanistic isolation of active versus passive modalities—which could induce fatigue or jeopardize safety in acutely debilitated postoperative patients—this hybrid approach accommodates the fluctuating physical capacity inherent to intensive care recovery. Patients can safely initiate therapy with passive contemplation and progressively scale their physical and cognitive engagement as their clinical status improves. Under this framework, the primary intervention metric remains defined by the total duration of hardware exposure, reflecting the cumulative dose of immersive cognitive distraction driven by patient autonomy, regardless of the specific software application selected.

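### The protocol says it will show which distraction mechanism works best, but Group 1 versus Group 2 estimates only the effect of adding optional games to passive VR

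*Protocol article*

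**What the plan says.** Three summary sections present the trial as a comparison of active with passive VR. The Abstract says that the methodology will "compare active VR immersion, passive VR contemplation, and conventional multimodal analgesia in a high-complexity surgical setting". The Specifications table (Value of the Protocol) adds that "the protocol helps identify which cognitive distraction mechanisms are most effective in modulating acute postoperative pain". The Background names active gaming and passive 360-degree video as two strategies and says that they are evaluated "to determine their respective impact on postoperative recovery".

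The section on Virtual reality interventions defines the arms. Group 2 receives standard care and a headset with passive video. Group 1 receives standard care and "VR headsets equipped with both the passive YouTube VR content and immersive interactive gaming experiences". The text then explains: "By intentionally allowing free transition between active and passive content", the design aims to "evaluate whether providing the additional option of interactivity yields superior clinical outcomes and higher protocol adherence" than the passive-only device. It gives fatigue and safety in weakened patients as the reason for this approach, "Rather than enforcing a rigid mechanistic isolation of active versus passive modalities". The intervention metric is total hardware time, "regardless of the specific software application selected".

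The section on Trial procedures and data collection makes the dose a continuous variable, the sum of minutes over all 15 sessions. The safety section still calls Group 1 the active arm, yet lets its patients begin with passive viewing. No minimum gaming time is stated. The Limitations section does not mention that the two modalities are mixed in Group 1.

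**The concern.** The document poses two different questions for the same pair of arms. One is whether active distraction works better than passive distraction. The other is whether offering games on top of passive video improves outcomes or adherence. The arms as defined can answer only the second, while the Abstract and the value statement announce the first.

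This governs what may be concluded. A null Group 1 versus Group 2 result could mean that games add nothing, or that few patients played them, and the exposure metric as defined could not tell these apart. A reader who relied on the Abstract would take the null as evidence that active distraction is no better than passive. The trial's declared purpose is to give early signals and variance estimates for definitive trials, so a mislabelled contrast could be carried into their design.

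**Working it through.** **1. The plan's own exposure figure.** Inputs: 45 minutes per session, three sessions a day, five days (Trial procedures and data collection; Clinical endpoints and blinding). 45 × 3 × 5 = 675 minutes, and 675 / 60 = 11.25 h over 15 sessions. This reproduces the stated maximum dose.

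**2. What that figure can distinguish.** Let G be minutes in games and V minutes in passive video. The plan's dose is G + V. Two Group 1 patients who complete every session in full:

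| Patient | G | V | Recorded dose |
|---|---|---|---|
| All video | 0 | 675 | 675 |
| All games | 675 | 0 | 675 |

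No stated rule excludes either patient, and the metric gives both the same value. The first patient's content is of the same type as that of Group 2.

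**3. What each contrast estimates.** The two VR arms share standard care, headset, passive content, session schedule and bedside supervision. They differ by randomisation in access to games.

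- Group 1 versus Group 2: the effect of adding the option of games to passive VR.
- Group 2 versus Group 3: the effect of passive VR, with its supervision, on top of standard care.
- Group 1 versus Group 3: the effect of a mixed package whose proportions the patient chooses.

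None of these isolates active gaming.

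**4. Illustration of dilution.** The documents give no active-versus-passive effect and no power calculation, so the effect d is assumed. The first value borrows the size of the cited overall VR effect (SMD −0.65), which is not an active-versus-passive effect. The second is a conventional large effect. Let f be the share of Group 1's time spent in games, and assume linear dilution, so the expected contrast is d × f. Power is for a two-sample t-test with 20 per arm and two-sided alpha 0.05 (the plan states 0.05 but not sidedness), with noncentrality d × f × √(20/2) on 20 + 20 − 2 = 38 degrees of freedom. For d = 0.65 and f = 0.5: 0.325 × 3.162 = 1.03, which gives power 0.171.

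| d | f = 1 | f = 0.75 | f = 0.5 | f = 0.25 |
|---|---|---|---|---|
| 0.65 | 0.517 | 0.324 | 0.171 | 0.079 |
| 0.80 | 0.693 | 0.456 | 0.234 | 0.095 |

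At f = 0 the expected difference due to content is zero. The smallest d with 80% power at f = 1 is (1.960 + 0.842) × √(2/20) = 0.89 by the normal approximation, or 0.91 by the t-test. The planned mixed model with surgical type as a covariate would shift these values. They show direction and rough size only.

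**The case against.** The strongest reply is that the design section already states the narrower question, calls Group 1 an enriched arm, and gives reasons for not separating the modalities. The value statement says only that the protocol helps to identify mechanisms, and it is neither an objective nor an analysis. The primary objective, preliminary efficacy of the VR protocol on opioid use and pain, is untouched. The flexible arm is a disclosed and reasoned choice, and nothing here asks for it to change. All of this stands, but it leaves two incompatible descriptions of one contrast, with the unsupported one in the parts most often read. The Background wording can be read as each strategy against control. Even so, Group 1 against control gives the effect of the mixed package, not of active gaming.

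A reader might infer more than the documents support:

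- That Group 1 versus Group 2 is uninterpretable, or that a positive result could not be credited to interactivity. It could be credited to the offer of interactive content, which is the randomised difference. It could not be assigned to a particular mechanism.
- That headset minutes are the trial's only metric. That is true of exposure alone. The outcomes are opioid consumption and pain scores, compared between randomised arms.
- That application use goes unrecorded. The section on Trial procedures and data collection mentions bedside forms for the events of each session. They are not shown and may hold this information.
- That a null will be reported as equivalence. No section plans this, and the Limitations section warns of low power and type II error. That warning concerns sample size and does not cover mixed content.

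**Conclusion.** Wrong as written. The summary sections claim a comparison of active with passive distraction, and the Specifications table claims insight into which mechanism works best. The arms as defined do not provide either. Group 1 versus Group 2 remains a sound randomised comparison of passive VR with and without optional games.

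The conclusion rests only on the text: shared passive content, free switching, no stated minimum of gaming, isolation expressly not enforced, and a dose that ignores the application. The recorded dose is compatible with any gaming time from 0 to 675 minutes in a patient who completes all sessions in full. The power figures depend on assumed effects and linear dilution, and the finding does not need them. Even with complete separation, 20 per arm reaches 80% power only for a difference of about 0.9 SD. If the forms do record application use, the reporting problem shrinks but the mechanism claim still fails. Time in games is chosen by patients and rises as their condition improves, so a comparison by content actually used would not be randomised.

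**What to change.** 1. Reword the Abstract, the Specifications table and the Background so that Group 1 versus Group 2 is the effect of adding optional interactive content to passive VR. Drop the claim about identifying mechanisms. Refer to Group 1 in the safety section in the same terms.
2. Split the exposure metric into game minutes and passive-video minutes per session on the existing bedside form, if this is not already captured. Keep the total as their sum.
3. Report Group 1's gaming share beside each Group 1 versus Group 2 estimate, labelled as descriptive and non-randomised.
4. State in advance that a null Group 1 versus Group 2 result will not be interpreted as equivalence of active and passive distraction.

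The cost is a narrower claim and one or two form fields, completed by the professional who is already at the bedside throughout each session. Arms, sample size and patient care stay as they are.

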## Background

The management of postoperative pain in cardiothoracic surgery remains a critical challenge, as inadequate analgesia more than doubles the risk of postoperative complications (OR 2.56), including respiratory dysfunction and prolonged hospitalization [1]. Furthermore, while opioids represent the analgesic cornerstone, their dose-dependent administration induces adverse events in approximately 20% of patients, precipitating significant morbidity such as respiratory depression, emesis, and long-term dependence [2].

This proposed protocol addresses the clinical need for innovative, non-pharmacological adjuncts to multimodal analgesia. Grounded in the limited capacity theory of attention, highly immersive distractors exhaust finite cognitive resources, modulating shared cortical networks [3] and triggering neurochemical responses, such as endorphin release, to effectively reduce perceived pain intensity [4].

Virtual Reality (VR) provides a superior level of immersion compared to traditional distraction methods, yielding up to an 88% decrease in postoperative pain [5]. Therefore, this study is designed as a proof-of-concept efficacy trial to standardize VR application in the Intensive Care Unit (ICU) setting, targeting patients (16–40 years old) undergoing cardiothoracic surgery. Our primary objective is to evaluate the preliminary clinical efficacy of this multi-session VR protocol on cumulative opioid consumption and pain intensity. It distinguishes itself by evaluating two digital strategies—active gaming, associated with the attenuation of cortical pain-related amplitudes [6], and passive 360° video contemplation—to determine their respective impact on postoperative recovery.

By establishing this early-stage framework, this protocol provides researchers and clinicians with a reproducible model for integrating digital health technology into the perioperative period, emphasizing technical feasibility, equipment hygiene, and patient safety, while gathering preliminary efficacy signals to guide future definitive trials.

## Study design and randomization

The VR-USP study follows a Prospective Randomized Open, Blinded Endpoint (PROBE) three-arm clinical trial design with a 1:1:1 allocation ratio. The trial protocol was reviewed and approved by the Institutional Review Board (Protocol Number: CAAE 74,181,523.0.0000.0068) and prospectively registered in a primary clinical trial registry (Registry Number: NCT07063394). To evaluate the intervention’s robustness within a diverse cardiothoracic population, a block randomization sequence, consisting of twenty fixed blocks of three, is generated by an independent statistician utilizing Microsoft Excel software. This pragmatic approach is selected to reflect real-world clinical heterogeneity, ensuring that the trial’s findings maintain high external validity for routine intensive care workflows. Allocation concealment is ensured through the use of sequentially numbered, opaque, and tamper-evident sealed envelopes, numbered from 1 to 60. These envelopes are stored in a locked cabinet controlled by an independent clinical nurse who has no contact with the trial participants. Furthermore, the specific envelope for each participant is only released to the research team after a designated investigator obtains the appropriate consent documents, including parental consent and minor assent for patients under 18 years of age, and enrolls the patient. Consequently, the recruiters remain blinded to the allocation sequence prior to inclusion, and the assigned intervention arm is revealed only post-enrollment, thereby maintaining appropriate allocation concealment.

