## Sample size and study population

The fundamental rationale relies on the limited capacity theory of attention, positing that highly immersive multisensory environments exhaust finite cognitive resources to mitigate acute pain perception [7]. Furthermore, as demonstrated by Lier et al., virtual reality yields significant overall analgesic efficacy (SMD = −0.65), with particularly robust effects observed among younger demographics [8]. Consequently, the trial enrollment focuses on 60 patients aged 16 to 40 years. Eligible procedures include cardiac and specific thoracic surgeries, such as pulmonary decortication, video-assisted thoracoscopic surgery (VATS), lung biopsy, and Nuss bar pectus excavatum repair.

As this trial is designed as an early-stage, proof-of-concept efficacy study in the specific context of cardiac surgery, a formal a priori power calculation for clinical efficacy is not performed. Instead, a pragmatic sample size of 20 patients per arm (total N = 60) is established. This sample size is aligned with phase IIa / proof-of-concept trials aimed at detecting large clinical effect sizes, evaluating the safety profile of the intervention, and providing initial estimates of variance (mean and standard deviation) to adequately power future, large-scale definitive multicenter trials.

While previous studies have demonstrated substantial effect sizes for VR analgesia in other surgical contexts, extrapolating those parameters to a three-arm, highly invasive cardiothoracic population is not methodologically sound for an a priori power calculation. Therefore, this sample size of 60 serves as a pragmatic and methodologically sound approach. It is sufficiently large to evaluate our primary feasibility metrics and safety profiles, while providing exploratory signals regarding the cumulative opioid consumption to inform future research.

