In parallel, as a crucial secondary clinical outcome, pain intensity is measured using the Visual Analogue Scale (VAS) at rest and during movement, which is specifically elicited by instructing the patient to take a deep breath. Evaluating dynamic pain represents the clinical gold standard, as joint practice guidelines from the American Pain Society and the American Society of Anesthesiologists emphasize that assessing pain during movement or activity is essential to accurately capture postoperative discomfort and guide functional recovery [21]. These VAS assessments are conducted at predefined and standardized time points throughout the day, ensuring temporal consistency across all three study arms. To clarify the Prospective Randomized Open, Blinded Endpoint (PROBE) design, we have explicitly defined the blinding status of all involved personnel. Due to the physical and highly visible nature of the Virtual Reality headsets, complete double-blinding is structurally impossible. Therefore, to mitigate detection and performance bias, a strict blinding matrix is established (Table 1).

**Table 1 tbl0001:** Blinding matrix for the PROBE design.

Role	Blinding Status	Justification / Mitigation Strategy
Participants	Unblinded	Inherent to the use of highly visible VR equipment.
VR Application Team	Unblinded	Researchers responsible for device setup and safety monitoring.
ICU Clinical Team	Unblinded	Cannot be blinded due to the shared, open ICU environment.
Pain Outcome Assessors	Blinded	Distinct staff exclusively assessing VAS. Patients are instructed daily not to discuss VR.
Statistician	Blinded	Data delivered with masked group codes (e.g., Group A, B, C).

By completely separating the personnel who administer the VR sessions from the clinical professionals who assess the Visual Analogue Scale (VAS) scores, the outcome assessors remain blinded to the assigned intervention. Additionally, the primary endpoint (cumulative opioid consumption) is quantified objectively via automated PCA pump logs and standardized medical records, structurally preventing expectancy bias from the outcome assessors.

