## Statistical analysis plan

The statistical analysis plan will be executed using SPSS software. Initially, continuous variables will be checked for normal distribution using the Shapiro-Wilk test. To compare baseline characteristics and cross-sectional continuous data among the three distinct groups, a One-Way ANOVA or Kruskal-Wallis test will be utilized, as appropriate. Furthermore, categorical baseline outcomes will be assessed through Chi-squared or Fisher's exact tests.

To account for unequal observation windows arising from early hospital discharge or varying ICU lengths of stay, the primary endpoint will be time-standardized. The absolute cumulative opioid consumption will be divided by the individual patient's exact observation time, yielding a standardized rate of Morphine Milligram Equivalents (MME) per 24 h. This primary outcome, along with the longitudinal secondary clinical outcomes (specifically the repeated Visual Analogue Scale scores evaluated at multiple time points), will be analyzed exclusively using Generalized Linear Mixed Models (GLMM). This advanced modeling accounts for intra-subject correlation over time. Crucially, to adjust for the inherent clinical heterogeneity between distinct surgical profiles (e.g., median sternotomy versus thoracic procedures like VATS or Nuss repair), the 'Surgical Type' will be included as a fixed-effect covariate in the model.

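### Fixed blocks of three for three arms leave at least 20 of 60 allocations deducible, so the statement that recruiters stay blinded to the sequence does not follow

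*Protocol article*

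**What the plan says.** The protocol article, under Study design and randomization, describes a "three-arm clinical trial design with a 1:1:1 allocation ratio" and "a block randomization sequence, consisting of twenty fixed blocks of three, is generated by an independent statistician". The list is held in "sequentially numbered, opaque, and tamper-evident sealed envelopes, numbered from 1 to 60". On release it says that "the specific envelope for each participant is only released to the research team after a designated investigator obtains the appropriate consent documents", and it concludes that "the recruiters remain blinded to the allocation sequence prior to inclusion".

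Under Clinical endpoints and blinding, Table 1 lists participants, the VR application team and the ICU clinical team as unblinded. The reason given for the ICU team is "Cannot be blinded due to the shared, open ICU environment". Recruiters and the enrolling investigator have no row in that table. The Limitations section says that the research team knows who uses a headset and that the trial has one centre.

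No stratification is described. The Statistical analysis plan section includes surgical type as a fixed effect, "to adjust for the inherent clinical heterogeneity between distinct surgical profiles".

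**The concern.** Opaque envelopes and a locked cabinet stop anyone from reading the next assignment. They do not stop anyone from working it out. Three is the smallest block possible for three arms at equal allocation, which makes it the most predictable. The size is constant and is printed in the article.

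Enrolment here involves discretion. The Trial procedures and data collection section treats willingness to consent as a filter for affinity with the technology. A recruiter who expects control next could delay an approach to a patient, or put less effort into it, on the basis of expected pain or keenness for VR. The blinded pain assessors, the masked statistician and the pump logs all act after enrolment and do not protect against this.

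**Working it through.** **Inputs.** Three arms at 1:1:1, twenty blocks of fixed size three, and one list of envelopes 1 to 60 (Study design and randomization); "a pragmatic sample size of 20 patients per arm (total N = 60) is established" (Sample size and study population); one centre (Limitations).

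**1. The plan's own figure.** 20 blocks × 3 = 60 envelopes, and 60 / 3 = 20 per arm. This reproduces.

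**2. Certain allocations.** With block size 3 and three arms, each block is an ordering of the three arms. Someone who knows the size and the earlier allocations in the block has three arms left at place 1, two at place 2 and one at place 3. Place 3 is certain in every block: 20 × 1 = 20 of 60 (33.3%). If the envelopes are used in order, these are the envelopes whose numbers are multiples of three.

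**3. Best-guess rate.** (1/3 + 1/2 + 1) / 3 = 61.1%, against 33.3% under unrestricted randomization.

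**4. VR versus control only.** Place 1 is never certain. Place 2 is certain when place 1 was control (probability 1/3), since both remaining places must then be VR. Place 3 is always certain. So (0 + 1/3 + 1) / 3 = 44.4%, and 60 × 0.444 = 26.7, about 27 of 60. This count needs only knowledge of who has a headset.

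**5. Other block schemes.** These are simulated. For the mixed sizes, the guesser knows the set of sizes but not their order, and updates optimally after each allocation.

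| Scheme | Certain, exact arm | Certain, VR v control | Best-guess rate |
|---|---|---|---|
| Fixed 3 (plan) | 33.3% (20 of 60) | 44.4% (about 27) | 61.1% |
| Fixed 6 | 20.0% (about 12) | 28.8% (about 17) | 56.1% |
| Fixed 9 | 12.8% (about 8) | 19.5% (about 12) | 52.1% |
| Random 3/6 | 8.6% (about 5) | 12.7% (about 8) | 57.6% |
| Random 6/9 | 5.0% (about 3) | 7.9% (about 5) | 53.9% |
| Random 3/6/9 | 3.7% (about 2) | 5.8% (about 3) | 55.2% |

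Randomly varying sizes remove most of the certainty. They lower the average guess rate much less.

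**6. Who holds the information.** Each envelope goes to the research team once the patient is enrolled, so the team learns every past allocation as it happens. VR use is also visible to unblinded staff in an open unit. The article gives the recruitment team and the bedside team different tasks, but states no rule that keeps past allocations from recruiters. The assurance of blinding therefore rests on the envelopes alone, and steps 2 to 4 show that they do not carry it.

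**The case against.** Several objections limit the point.

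- **Concealment has not failed altogether.** A reader might infer that anyone who has seen the last two allocations knows the next. That is true only when those two fill places 1 and 2 of the same block, so the observer must also know the block boundary. The first place of each block stays concealed, and for 40 of 60 places the exact arm is not certain.
- **A visible headset does not identify the arm.** Group 1 may use the same passive content as Group 2 and may begin with it. What is seen in the ICU separates VR from control, not Group 1 from Group 2. The 20 of 60 and the 61% need the actual arm, which the research team has from the envelopes. The 27 of 60 does not need it.
- **Postoperative pain may not be known at enrolment.** Screening is preoperative and the time of randomization is not stated. Selection could act on expected pain or on interest, not necessarily on observed pain.
- **Not all such bias is beyond analysis.** Selection on a recorded factor such as surgical type is at least partly handled by the adjusted model. The problem that remains is selection on unmeasured factors.
- **The trial is a proof-of-concept study.** That lowers the stakes, but its stated purpose includes efficacy signals to guide later trials, and selection would distort those too.

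A reader might also infer that the list is wrong because it is not stratified by a factor that the model adjusts for. The document does not support that: adjustment without stratification is valid, and chance imbalance in an adjusted covariate costs some precision without biasing the comparison. The case mix is not given. At an assumed 50% cardiac share, the largest and smallest arms differ by 5 or more cardiac patients of 20 in about 32% of trials (17% at a 20% share). For one pre-named pair of arms the figure at 50% is about 15%.

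**Conclusion.** The point stands for predictability. Concealment is not protected for at least 20 of 60 allocations, with a best-guess rate of 61% against 33%; for VR versus control, about 27 of 60 are determined. The claim that recruiters remain blinded does not follow from the procedures described and needs correcting.

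These counts assume an observer who knows the block size, tracks the block boundary and knows the earlier allocations (for the 27, only who had a headset). The documents place that information with the research team and do not bar recruiters from it. They do not show that anyone has used it, so this is an open route to selection bias and not evidence of bias. It should be closed before more patients are enrolled, since later analysis does not reliably undo selection on unmeasured factors.

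The absence of stratification is not an error and forms no part of this conclusion.

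**What to change.** 1. Have the independent statistician regenerate the list for all unopened envelopes with randomly varying block sizes, for example 3, 6 and 9.
2. Keep the new sizes and their order out of site documents and away from all recruiting staff.
3. Withhold past allocations from recruiters as far as an open unit allows, and add recruiters and the enrolling investigator to Table 1 with their blinding status.
4. Correct the concealment statement under Study design and randomization. If envelopes have already been opened under fixed blocks of three, report how many.

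Certain allocations fall from 20 to about 2 of 60. The hit rate falls only from 61% to about 55%, so step 3 matters as well as step 1.

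The cost is a new list and a short protocol change, with no extra patients. Arm totals may no longer be exactly 20 each: an incomplete block of 9 can leave a gap of 3.

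Stratifying by cardiac versus thoracic surgery is optional. With two strata and 3/6/9 blocks, at an assumed 50% cardiac share, the total gap between arms is 3 or more in about 9% of trials. Using fixed blocks of three within strata would leave the predictability in place.
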